# Evaluation of the “safe multidisciplinary app-assisted remote patient-self-testing (SMART) model” for warfarin home management during the COVID-19 pandemic: study protocol of a multi-center randomized controlled trial

**DOI:** 10.1186/s12913-021-06882-7

**Published:** 2021-08-26

**Keywords:** Warfarin, Patient self-testing, Safety, Effectiveness, Cost-effectiveness

## Abstract

**Background:**

Warfarin treatment requires frequent monitoring of INR (international normalized ratio) to adjust dosage in a therapeutic range. In China, patients living in small towns usually go to tertiary hospitals to get warfarin monitoring and dosing, resulting in low frequencies of follow-ups and high incidence of complications. Influenced by the COVID-19 pandemic, patients on warfarin have further reduced their visits to healthcare institutions. While patient self-testing (PST) via using a point-of-care testing device for INR measuring at home has been widely used in developed countries and demonstrated improved clinical outcomes compared to usual care in clinics, it is rarely applied in developing countries, including China. This proposed study will develop and assess the “Safe Multidisciplinary App-assisted Remote patient-self-Testing (SMART) model” for warfarin home management in China during the COVID-19 pandemic.

**Methods:**

This is a multi-center randomized controlled trial. We will carry out the study in three county hospitals, three small tertiary hospitals and three large tertiary hospitals with anticoagulation clinics in Hunan province of China. Eligible patients will be randomly assigned to the SMART model group (*n* = 360) or the control group (usual care clinic group, *n* = 360; anticoagulation clinic group, *n* = 120). Patients in the SMART model group do PST at home once every two to 4 weeks. Controls receive usual care in the clinics. All the patients will be followed up through outpatient clinics, phone call or online interviews at the 3rd, 6th, 9th and 12th month. The percentage of time in therapeutic range (TTR), incidence of warfarin associated major bleeding and thromboembolic events and costs will be compared between the SMART model group and control groups.

**Discussion:**

Patients in the SMART model group would show improved TTR, lower incidence of complications and better quality of life compared to the control groups. Our design, implementation and usage of the SMART model will provide experience and evidence in developing a novel model for chronic disease management to solve the problem of healthcare service maldistribution, an issue particularly obvious in developing countries during the COVID-19 pandemic.

**Trial registration:**

ChiCTR, ChiCTR 2000038984. Registered 11 October, 2020.

## Background

In line with the increasing aging population, the incidence and prevalence of atrial fibrillation (AF) and other thromboembolic diseases have dramatically increased and become a significant health problem worldwide [1]. Patients with these conditions should take long-term or lifelong anticoagulant drugs to prevent or treat thrombosis. It’s estimated that at least 0.6% of people in China need anticoagulation therapy [2, 3].

Although the new oral anticoagulants (NOACs) have been used as alternatives to warfarin due to good safety and less monitoring, warfarin remains the first line anticoagulant in certain conditions, including mechanical heart valve replacement, severe mitral stenosis, renal failure and etc. In addition, anticoagulant choice is impacted by patients’ individual preference, insurance allowance and personal economic situation. Therefore, warfarin will continue to be widely used across the world.

Warfarin treatment is cheap and effective, but requires frequent monitoring to adjust dosage under professional guidance. In China, patients and families from rural locations often need to travel several hours to tertiary hospitals in big cities to get quality warfarin monitoring and dosing, resulting in poor compliance, limited monitoring frequency, high incidence of warfarin related complications and increased costs. During the COVID-19 pandemic, many patients with chronic diseases, including patients on warfarin, have reduced their visits to hospitals due to the social distancing policy and shortage of medical resources.

In China, the percentage of time in therapeutic range (TTR, a tool of measuring warfarin treatment effects) was less than 40%, which was significantly lower than that of 62% in western countries [4]. Clinical observation studies found that warfarin associated ischemic stroke and intracranial bleeding were respectively 5.23 and 2.94% in patients from China, significantly higher than patients from the rest of the world (2.94 and 0.63%, respectively) [5]. In warfarin-treated patients in China, the median in-hospital direct cost per patient was about $3, 000 for thrombosis and $4, 500 for intracranial hemorrhage [6]. These data suggest that warfarin management in China needs further improvement. An investigation study launched by the PI using the Andersen’s Health Services Utilization Behavioral Model in 469 patients on warfarin indicated that long time and high cost for travel, low family income, low quality of warfarin monitoring and dosing in local hospitals were dominant reasons for missing follow-ups (data not published yet).

Anticoagulation clinics (AC) have been proved safer and more effective than usual care in warfarin management [7, 8], but there are only about 50 ACs located in big cities of China (mainly run in a physician-pharmacist cooperative AC pattern) at present. The number of ACs is too low, and it is not easy to open more ACs due to limitation of health care professionals and longtime education.

Point-of-care testing (POCT) device designed for measuring INR by patients or their families was first developed in 1980s in America [9] and then widely used in many developed countries. Compared to traditional laboratory INR test in outpatient clinics, POCT has great advantages in convenient home testing and fast result reporting. Soon patient self-testing (PST) for warfarin home management by using POCT devices and telehealth has been rapidly applied in developed countries. Although the PST model of warfarin management has demonstrated improvement of clinical outcomes compared to usual care clinics and anticoagulation clinics [10], it is rarely applied in developing countries, including China.

The COVID-19 pandemic has motivated significant changes to health-care system, many of which will have a lasting impact. Telehealth or telemedicine, which is defined as the use of medical information over a spatial distance through electronic communication to improve a patient’s health, has been widely implemented during and after the COVID-19 pandemic all over the world [11, 12]. In the early stage of the pandemic, we had integrated telehealth and INR testing POCT device to guide a few patients to monitor INR and adjust warfarin dosage at home. Those patients were managed very well with improved TTR and satisfaction.

In order to improve warfarin management in China during the COVID-19 pandemic, we have proposed a novel management mode called the “Safe Multidisciplinary App-assisted Remote patient-self-Testing (SMART) model” for warfarin home management. Our team has developed a mobile phone based app which called “XY” app, (XY is abbreviated for Xiangya Second hospital) to efficiently assist managing warfarin with different strategies based on patients’ risks of bleeding or thrombosis. Moreover, we will use the resources of medical alliance (of which tertiary hospitals collaborate with local hospitals for patient treatment and referral) to train local health care providers and establish multidisciplinary teams to manage patients together.

### Aim

This study aims to improve patients’ medical outcomes and quality of life, reducing patients’ burden of frequent follow ups in tertiary hospitals, and decreasing patients’ dependence on health care professionals to a certain extent by implementing the SMART model to manage patients on warfarin during the COVID-19 pandemic. Moreover, our study will provide experiences of telehealth implementation during and after the COVID-19 pandemic, which would be particularly helpful for areas with uneven medical quality. Ultimately, we expect to expand the SMART model to manage other chronic diseases.

## Methods/design

### Study design

This is a multi-center randomized controlled trial. We will carry out the study in three large tertiary hospitals with anticoagulation clinics, three small tertiary hospitals and three county hospitals in Hunan province of China. Eligible patients will be randomly assigned to the SMART model group or the control group (usual care clinic and anticoagulation clinic). Patients in the SMART model group do PST at home once every two to 4 weeks. Control patients receive usual care without intervention. All the patients will be followed up through outpatient clinics, phone call or online interviews at the 3rd, 6th, 9th and 12th month. The percentage of time in therapeutic range (TTR), incidence of warfarin associated major bleeding and thromboembolic events and costs will be compared between the SMART model group and control groups. Figure 1 describes the study design.

**Fig. 1 Fig1:**
[figure not shown]
Flow chart of the study

### Study participants and inclusion criteria

Patients eligible for this project have to comply with all of the requirements below: are expected to be on warfarin treatment for the duration of at least 12 months, accept the study protocol and randomization, and sign an informed consent. Patients who fall into any of the following criteria are excluded in this project, including pregnancy or plan to get pregnant in 18 months, had experienced a bleeding complication requiring treatment in the past 6 months, are unable to attend a hospital in 6 hours, renal failure (hemodialysis or glomerular filtration rate < 10 mL/min), dementia or unstable psychiatric conditions or receiving treatment for cancer.

A patient who has been enrolled in the project will be considered as a dropout if meets any of the following criteria and the reason will be recorded: the patient decides to withdraw for any reason; the patient in the SMART model group does not follow the health-care professionals’ instruction for at least twice; the researcher considers the patient is no longer physically and/or psychologically fit to remain in the study. The impact of dropouts on statistical analyses, including intention to treat, will be used by carrying the last observation forward.

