#### Enrolling patients

Patients on warfarin attending the participated hospitals will be invited to join in the study. If the patients show interest, then the design and rationale of the study will be explained. The research staff will identify which patients are potentially suitable candidates for the study. After the eligible patients agree and sign the informed consents, the patients will be randomly assigned to either the SMART model group or the control group according to the protocol.

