#### Baseline interview

All the participated patients will be required to complete a survey either via an online survey through their mobile phone or via a printed brochure. The contents of the survey contain three parts, including patients’ clinical parameters (warfarin indication, start date of warfarin, warfarin dosage, previous TTR, history of thrombosis or major bleeding, concomitant diseases and medicine), behaviour indicators (warfarin knowledge, anticoagulant compliance, treatment behavior and quality of life) and costs on warfarin related treatment.

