**Dangerous**	Patients have to meet one of the conditions below: 1. INR is < 1.5 or > 4.5 2. Patients have major bleeding 3. Patients have thrombosis 4. Patients have other severe symptoms, such as dyspnea, severe headache	The health care providers will call the patients immediately. Patients will be advised to go to the local hospital or tertiary hospital for further treatment based on their risks.

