#### Follow-up visits and data collection

Each of the enrolled patients has to record his/her warfarin related information in a printed monitoring handbook, including INR results, warfarin dosage, other medicine, diet change, new disease, and thrombosis or bleeding events (if occurs). All the patients are required to receive follow-ups at the 3rd, 6th, 9th and 12th month through outpatient clinic visits, telephone or online interviews. At each follow-up time-point, the research stuff will collect the warfarin related information. Double data entry will be carried out to ensure data accuracy and data will be kept in encrypted mobile hard disks to protect patients’ privacy. Only the corresponding author has access to the final trial dataset. As shown in Table 3, patients are required to provide the information of warfarin dosage and INR results, the numbers of going to the outpatient clinics or inpatient treatment due to warfarin, quality of life as measured by the health index scale (EQ-5D-3L) [16], and the related treatment costs. At baseline and the last time visit, patients are required to fill in the Morisky anticoagulant compliance questionnaire [14] and the oral anticoagulation knowledge test [15]. An anticoagulation satisfaction survey by using the Duke Anticoagulation Satisfaction Scale [17] will be conducted to all the patients at the end of the study. The research staff will send text messages to remind the patients for follow-ups and all the participated patients will receive certain amount of compensation fees to sustain their involvement in the study.

**Table 3 Tab3:** Measurement domains, survey methods and collection time-points

Variable	Component	Measurement methods	Baseline	3rd M	6th M	9th M	12th M
**Socio-demographic parameters**	Gender, age, telephone, address, education, occupation and annual income	Face-to-face interview	√				
**Clinical parameters**	Height, weight, warfarin indication, start date of warfarin, warfarin dosage, TTR calculated by INR tests in the preceding 12 months, history of thrombosis or major bleeding, concomitant diseases and medicine Warfarin dosage, INR, bleeding or thrombosis, other clinical adverse events	Face-to-face interview	√				
		Face-to-face interview, telephone or online interview		√	√	√	√
**Behaviour parameters**	Anticoagulant compliance, warfarin knowledge,	Morisky Anticoagulant Compliance Questionnaire [14], Oral Anticoagulation Knowledge (OAK) Test [15]	√				√

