### Outcomes

#### Primary outcome measure

The difference in TTR between the SMART model group and the control group during the 12 month period of study.

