#### Secondary outcome measures

The numbers of INR results indicating excessive under-coagulation or over-anticoagulation (INR < 1.5 or INR > 5.0).Serious adverse clinical events (clinical relevant non-major bleeding, major bleeding, thrombosis or death)Patients’ quality of life.Costs on warfarin management.

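### Recent warfarin starters can enter, and the stated comparisons of TTR and of INR results below 1.5 do not adjust for this, although the start date is collected

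*Protocol article*

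**What the plan says.** Under Study participants and inclusion criteria, the protocol article lists three requirements. Patients "are expected to be on warfarin treatment for the duration of at least 12 months", and they must "accept the study protocol and randomization, and sign an informed consent". Neither these nor the exclusions mention time already on warfarin, a stable dose or a minimum number of earlier INRs. The recruitment pool is equally open: "Patients on warfarin attending the participated hospitals will be invited to join in the study" (Enrolling patients).

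The baseline survey asks for "start date of warfarin, warfarin dosage, previous TTR", and Table 3 specifies "TTR calculated by INR tests in the preceding 12 months".

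The primary outcome is "The difference in TTR between the SMART model group and the control group during the 12 month period of study". One secondary outcome is the number of results with "INR < 1.5 or INR > 5.0". Neither outcome leaves out a start-up period. Data analyses names the t-test or Mann–Whitney test for comparing SMART with control, the Rosendaal method for TTR, and a mixed model and survival analysis for follow-up data. It names no covariate for the TTR or INR comparisons.

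**The concern.** INR takes time to reach range after warfarin is started, whichever model manages the patient. For someone who enters in the first weeks of treatment, part of the 12-month TTR and some of the INR results below 1.5 reflect the start of the drug as well as the quality of monitoring. The arms then hold a mixture of recent and established users who probably differ in expected TTR. The stated tests ignore that difference, so it stays in the error variance, and any chance imbalance between arms passes into the estimate.

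Baseline TTR would be the natural covariate to absorb this, but it is weakest for these patients. A patient with days or a few weeks of treatment has few INRs in the look-back window, or none. Start date is complete where baseline TTR is not.

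**Working it through.** **What the text permits.** Entry requires expected future use and current use of any length. Baseline TTR looks back up to 12 months. Both outcomes count from entry. A patient on warfarin for one week meets every listed criterion, contributes titration INRs to both outcomes, and has almost no history for baseline TTR.

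**Inputs from the protocol.** Target difference 5 TTR points, 80% power, P = 0.05, 31 per group before dropout (Sample size determination); two-tailed tests (Data analyses); 120 per arm at each hospital level (Randomization); 360 SMART and 360 usual-care patients in all (Abstract).

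**Assumptions, not in the protocol.** Titration lasts 4 to 8 of 52 weeks. TTR is 20% during titration and 50% afterwards. The share of recent starters averages 35%, and a 10-point imbalance means 30% in one arm and 40% in the other.

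**The plan's own figure.** No SD is given, so 31 per group cannot be reproduced directly. Solved backwards, SD = 5 / [(1.960 + 0.842) × √(2/31)] = 7.03 points. I use 7 below, and 20 as an assumed larger value.

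**Loss in one recent starter's 12-month TTR.** Loss = (weeks/52) × (50 − 20).
- 4 weeks: 4/52 × 30 = 2.3 points
- 8 weeks: 8/52 × 30 = 4.6 points

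**Shift in the arm difference for a 10-point imbalance.** 0.10 × 2.3 = 0.23 and 0.10 × 4.6 = 0.46, so about 0.2 to 0.5 points.

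**How likely that imbalance is.** SE of the difference in shares = √(2 × 0.35 × 0.65 / n).
- n = 120 per arm: 6.2 points, so 10 points is 1.6 SE
- n = 360 per arm: 3.6 points, so 10 points is 2.8 SE

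A one-SE imbalance at 360 per arm shifts the TTR difference by 0.036 × 2.3 = 0.08 to 0.036 × 4.6 = 0.16 points.

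**Added variance.** Added variance = 0.35 × 0.65 × loss², which is 1.2 to 4.8.

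| SD without recent starters | SD with them | n per group for 5 points |
|---|---|---|
| 7 | 7.09 to 7.34 | 31 becomes 32 to 34 |
| 20 | 20.03 to 20.12 | 252 becomes 252 to 255 |

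**Wider assumptions.** With 4 to 12 weeks, a deficit of 20 to 40 points and 10% to 50% recent starters, the loss per recent starter is 1.5 to 9.2 points. The SD of chance imbalance at 120 per arm is then 0.06 to 0.6 TTR points. At SD 7 the required n is 31 to 45, and at SD 20 it is 252 to 265.

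No similar calculation is possible for the count of INR results below 1.5. The protocol gives neither an expected count nor a testing schedule for the control arms.

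**The case against.** The case against is strong on several points, and most of it stands.

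- A reader might infer that baseline TTR requires 12 months of earlier INRs and so contradicts the eligibility rule. Table 3 describes a look-back window, not a required length of history. A patient with several months of INRs has a usable value; only very recent starters do not. No stated analysis uses baseline TTR, so none fails without it.
- A reader might infer a biased primary result, because a loss of 2.3 to 4.6 points per patient is close to the 5-point target. That loss falls on recent starters in every arm. Only the imbalance between arms reaches the difference, and it is small.
- A reader might infer that titration results would dominate the count of INRs below 1.5. The protocol gives no share of recent starters and no counts, so this cannot be shown. SMART patients retest within days after an out-of-range INR with a dose change, while control testing is left alone, so numbers of results may differ between arms. That applies to all patients and is a separate question.
- Table 2 uses "INR is < 1.5 or > 4.5" as a triage condition regardless of time since start. This is clinical management and shows no contradiction on the present point.
- A broad population is a legitimate choice. Early dose adjustment is part of what the model manages, and removing it changes the question.
- Covariates and counting rules may be in a full protocol or SAP that is not shown.

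What remains is narrower. The article does state how the arms will be compared. Those tests leave unused a baseline value that is already recorded and probably prognostic for both outcomes.

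**Conclusion.** The point holds in limited form. Recent starters can enter, their titration INRs count in TTR and in the count of results below 1.5, and their baseline TTR is thin or missing. This does not bias the primary comparison systematically. It adds a little variance and some chance imbalance: about 0.2 to 0.5 TTR points for a 10-point imbalance, under assumed titration of 4 to 8 weeks at TTR 20% versus 50% afterwards. An imbalance that large would be unusual at 360 per arm. The true size depends on the share of recent starters, which the documents do not give. The count of low INRs may be more sensitive, but the documents allow no figure for it.

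**What to change.** In Data analyses, state that the SMART-versus-control comparisons of TTR and of INR results below 1.5 are adjusted for recent versus established warfarin use. Define the two groups from the start date already collected at baseline, with one cut-off fixed in advance and applied in every arm. A linear model for TTR and a count model for the low INR results would serve. Patients are on warfarin when invited, so the start date precedes randomization and cannot depend on allocation.

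Add one sensitivity analysis in which TTR and the low INR count begin a fixed number of weeks after the warfarin start date, by the same rule in every arm. Keep the full 12 months as the main analysis, so that the question does not change.

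The cost is a little more analysis work and no new data; in the sensitivity analysis only, recent starters contribute less follow-up. A minimum prior duration for eligibility is an option for the sponsor, not a required correction. It would narrow the population, and since recruitment began in March 2021 it could apply only to patients still to be enrolled.

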#### Randomization

In low and medium level hospitals, only the UC group is used as the control group, thus eligible patients on warfarin will be randomly assigned to either the SMART model group or the UC group. While in the high level hospitals, both AC and UC are used as the control groups, thus eligible patients will be randomly allocated to the SMART model group, the AC group or the UC group. For each level of the three hospitals, a total of 120 patients in each arm will be enrolled. The flow chart of patients’ grouping and allocation is shown in Fig. 2. Patients’ randomization will be carried out by research staff using a standard protocol available in the website (http://stattrek.com/statistics/random-number-generator.aspx).

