#### Educating and training patients

All the enrolled patients will attend a warfarin education session by the research team after they sign the informed contents. The educational courses will include the mechanism of action of warfarin, blood tests of INR and target ranges, follow-up frequencies, potential signs and symptoms of over-coagulation and under-anticoagulation, drug/food interactions with warfarin, lifestyle, missed doses, over doses, adverse events treatment, etc. All the above-mentioned knowledge will be printed out and given to patients for home study. For patients allocated to the SMART model group, they will further attend a training program in groups of less than three people. They will learn how to use the POCT device, as well as report their INR results and receive instruction of warfarin dosage and follow-up dates through the XY app. Later, patients are required to use the POCT device to perform at least two reproducible INR measurements under the research staff’s supervision. These results will be compared with the laboratory INR measurement from a venous blood sample. If there are wide differences (> 0.3 INR units) between the POCT and laboratory INR tests, patients will be excluded from the study [13]. Patients or their guardians who fail to use the XY app to report data will also be excluded from the study.

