#### Data analyses

We will report continuous variables as means ± SD and categorical variables as proportions. Data will be checked for normal distribution by means of the Kolmogorov–Smirnov’s test. In compliance with the distribution of data, Student’s t-test or Mann–Whitney’s U-test will be used for comparisons between the SMART model group and control group. Chi-square or Fisher’s exact tests will be used to compare between the SMART model group and control group with respect to categorical data. The control of anticoagulation will be assessed by evaluating TTR with the Rosendaal method [18] in each arm. The follow-up assessment data will be analyzed using Generalized Linear Mixed Model and survival analysis. *P* ≤ 0.05 is considered statistically significant. All tests are two tailed. From the perspective of health-care payer, we will conduct a cost-effectiveness analysis to assess the economic impact of the SMART model for warfarin home management. A Markov model, a half-cycle correction and a discount of 5% will be constructed or used to estimate the total costs and quality-adjusted life-years (QALYs) over the 2-year period (the outcomes beyond the observation period will be predicted according to the results obtained in the study). We will collect the direct and indirect costs of each enrolled patient on warfarin, evaluate their quality of life through EQ-5D-3L utility value from data provided by patients, calculate QALYs, and analyze the effects of multiple variables by the Linear Mixed Effects Model. The direct costs include laboratory INR test fees in the control groups (or POCT fees in the SMART model group), outpatient clinic visit fees (or supervision fees in the SMART model group), hospitalization fees and emergency room visit fees. The indirect costs include deducted income due to absence of working, traffic fees and accommodation fees. Because warfarin is very cheap, the medication fee of warfarin is not calculated in each group. The incremental cost effectiveness ratio (ICER) will be calculated according to the total costs and QALYs, and one-way and probabilistic analyses will be performed to verify the stability of the model.

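### A patient judged unfit after a stroke or major bleed becomes a dropout with the last value carried forward, so what follows the event may be lost from the safety, quality-of-life and cost outcomes

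*Protocol article*

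**What the plan says.** The protocol article, under Study participants and inclusion criteria, lists when an enrolled patient counts as a dropout: "A patient who has been enrolled in the project will be considered as a dropout if meets any of the following criteria". One criterion, not restricted to any arm, is that "the researcher considers the patient is no longer physically and/or psychologically fit to remain in the study". It does not define fitness and does not exempt patients who have just had an outcome event. The handling rule follows directly: "The impact of dropouts on statistical analyses, including intention to treat, will be used by carrying the last observation forward".

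On who knows the allocation, the Randomization section says "randomization will be carried out by research staff using a standard protocol available in the website". Under Educating and training patients, those allocated to SMART must "perform at least two reproducible INR measurements under the research staff’s supervision". No blinding is described.

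The outcomes concerned are the secondary outcome "Serious adverse clinical events (clinical relevant non-major bleeding, major bleeding, thrombosis or death" (the list closes there), quality of life and costs. For the economic analysis, the Data analyses section plans to "evaluate their quality of life through EQ-5D-3L utility value from data provided by patients, calculate QALYs". The same section names a generalized linear mixed model and survival analysis for the follow-up data, and a Markov model over 2 years that predicts beyond the observation period from the study results. Follow-up visits and data collection schedules contacts at months 3, 6, 9 and 12 by clinic visit, telephone or online interview.

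**The concern.** Disabling stroke and major bleeding are outcomes of the trial, and they are also obvious ways for a patient to become physically unfit. The criterion therefore allows follow-up to end because of the outcome that follow-up is meant to measure. Take a patient with a stroke in month 5 who is then judged unfit. The last completed contact is month 3, so a literal carry-forward fills months 6, 9 and 12 with EQ-5D-3L and cost values from before the stroke. A later death or second event may not be collected at all.

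The judgement is left to the researcher, who probably knows the arm, so the readiness to withdraw patients may differ between arms. The comparison of quality of life, costs and QALYs, and the extrapolation built on it, would then depend partly on withdrawal decisions and not only on the patients' course.

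**Working it through.** The plan gives no figure of its own for this point. The sample size rests on TTR, and the 10% dropout allowance is not split by reason. The check is therefore an illustration, with assumptions marked.

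**1. One affected patient.** Assumed: utility 0.85 before the event, a lower value u afterwards, event just after the month-3 contact, QALYs by the trapezoidal rule over contacts at 0, 3, 6, 9 and 12 months.
- With continued follow-up: 0.25 × 0.85 + 0.25 × (0.85 + u)/2 + 0.5 × u = 0.31875 + 0.625u. This gives 0.725 for u = 0.65, 0.631 for u = 0.50 and 0.506 for u = 0.30.
- With carry-forward: 0.850.
- Overstatement: 0.625 × (0.85 − u) = 0.125 to 0.344. With death (u = 0 from month 6) it is 0.531.
- If the last contact was month 9: 0.125 × (0.85 − u) = 0.025 to 0.069.

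**2. Mean of one arm.** From the Background section: ischemic stroke 5.23% and intracranial bleeding 2.94% in Chinese patients on warfarin. No time base is given; 12 months is assumed.
- Events: 360 × (0.0523 + 0.0294) = 360 × 0.0817 = 29.4 in a group of 360, and 120 × 0.0817 = 9.8 in the anticoagulation clinic group.
- Assumed: 25 to 75% of these patients are judged unfit, half a year remains on average, and utility falls by 0.2 to 0.4.
- Low end: 0.0817 × 0.25 × 0.5 × 0.2 = 0.0020 QALY per randomised patient.
- High end: 0.0817 × 0.75 × 0.5 × 0.4 = 0.0123.

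**3. Difference between arms.** The between-arm bias is the difference of two such one-arm biases, so under these assumptions it cannot exceed the larger of them. The Discussion cites 50% fewer thromboembolic events with home management and similar safety for major bleeding. Applied here, the SMART rate would be 0.0523 × 0.5 + 0.0294 = 0.05555.
- Equal withdrawal shares: (0.0817 − 0.05555) × (0.25 to 0.75) × 0.5 × (0.2 to 0.4) = 0.0007 to 0.0039. More harm is hidden in the control arm, which dilutes a SMART benefit.
- SMART withdraws 75% and control 25%: (0.05555 × 0.75 − 0.0817 × 0.25) × 0.5 × (0.2 to 0.4) = 0.0021 to 0.0042 in the opposite direction, in favour of SMART.

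The sign therefore depends on event and withdrawal rates that the document does not give.

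**The case against.** A withdrawal clause at the investigator's discretion is routine, and an article may leave data collection after withdrawal to its full protocol. The article also says that all patients are followed at the four time points, and nowhere states that follow-up of a dropout stops. This is fair as far as it goes: the end of follow-up is an inference from the criterion's reference to staying in the study and from the need to carry values forward. But the dropout criterion and the carry-forward rule are both stated, and together they give a wrong value when applied as written. That is more than missing detail.

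A reader might infer three stronger things that the documents do not support.
- *That the stroke or bleed itself disappears.* It precedes the dropout, is a secondary outcome, belongs in the patient's handbook, and the reason for dropout is recorded.
- *That the patient is counted as alive and free of further events to month 12.* The Data analyses section plans survival analysis, in which a dropout would normally be censored. The problem there is informative censoring.
- *That the 3,000 and 4,500 dollars in the Background section measure the cost that goes missing.* They are in-hospital costs of the thrombosis or intracranial hemorrhage itself, which comes before the dropout and can still be recorded.

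It also stands that the article does not say how carried-forward values would enter the Markov model, and that most inputs to the size are assumed.

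**Conclusion.** The point holds as a defect in the stated dropout rule, and it is worth correcting. Nothing in the text compels a researcher to withdraw a patient after a stroke or bleed, but the text allows it, in every arm and without a definition of fitness. That the researcher knows the allocation is an inference, though a sound one, from research staff doing the randomisation and supervising the device training that only SMART patients receive.

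The damage falls mainly on the course after a serious event: later events and deaths, quality of life, costs and QALYs. The primary TTR is much less exposed. For a single affected patient the overstatement is 0.025 to 0.344 QALY under the assumed utilities, and 0.531 in the death scenario. Averaged over one arm it is about 0.002 to 0.012 QALY per patient. These ranges rest on an assumed 12-month time base, withdrawal share, timing and utility drop. Between arms the bias is smaller and may go either way, so it should not be presented as favouring SMART.

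**What to change.** Under Study participants and inclusion criteria, separate stopping study procedures from leaving follow-up. State that in every arm a patient judged no longer fit stays in the planned month 3, 6, 9 and 12 contacts for events, vital status, EQ-5D-3L and costs, by clinic, telephone or online and through a proxy if needed, unless consent is withdrawn. The wording must make sense for usual care and anticoagulation clinic patients too, so it cannot refer only to stopping SMART procedures.

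In the sentence on dropouts, exclude carrying pre-event EQ-5D-3L or cost values past a serious event, and set utility to 0 from the date of death. This concerns data collection and analysis only and leaves treatment decisions untouched.

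The contacts are already scheduled. The cost is a small number of proxy-reported forms and a protocol amendment. Recruitment began in March 2021 (Trial status), so the amendment needs ethics approval and patients must be informed, as the Data monitoring section provides. It should be made soon, because data that are not collected cannot be recovered by a later analysis plan.
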